##### Participant timeline

Informed consent to participate in the study will be obtained from the selected eligible participants (clusters, social groups and providers) before clusters are randomly allocated into the three study arms. The main study outcomes will then be measured through a baseline household survey and an end-of-study household survey 3 months after the end of the intervention. The participant timeline is depicted in accordance with the Standard Protocol Items: Recommendations for Interventional Trials (SPIRIT) guideline (see Fig. 1).

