### Measurement of study outcomes

#### Population-based household survey

The survey questionnaire was adopted from the 2015 NMIS [15] woman’s questionnaire and was modified to collect data on both the primary outcome and community-level secondary outcomes. The questionnaire will be pre-tested in non-participating clusters before the survey. Interviewers will be recruited and trained over a 1-week period to administer the questionnaire. The training of the interviewers will include a detailed review and explanation of the questionnaire items, interview techniques, how to provide information to household respondents about the survey, how to obtain consent, the translation of key words in the questionnaire to local language and how to administer the questionnaire. The baseline survey will be carried out before the intervention (see Fig. 1) to collect data for the assessment of the level of demand (use and/or request) for MRDT among community members with fever or malaria-like illness in Ebonyi state. A section of the questionnaire will collect data on the determinants of the demand for MRDT. The end-of-study survey will be carried out 3 months after the end of the intervention (see Fig. 1) to collect data for the evaluation of the effects of the interventions on the demand for MRDT among community members.

The interviewers will be accompanied by research supervisors at the start of the baseline survey for monitoring and supportive supervision. This will be followed by a visit at least once weekly for monitoring and supportive supervision. The household survey questionnaire is designed to collect data about the following items from the respondent female head of household (the mother of the house or female primary care giver):
Basic socio-demographic characteristics (of the respondent and of eligible household members reported to have had fever/malaria-like illness in the preceding 2 weeks)Fever/malaria-like illness management including care seeking and demand for MRDTThe respondent’s knowledge and opinions about malaria and malaria diagnosisThe determinants of the demand for MRDT

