#### Randomization

Randomization will be done using Stata version 12 (Stata Corp, College Station, TX, USA). A statistician that will not otherwise take part in the study will use stratified randomization to assign the 18 clusters across the 3 strata to the 3 treatment arms after written consent is obtained from all recruited participants. The six clusters within each stratum will be randomly allocated to the three study arms in the ratio of 2:2:2 using a programme written in Stata. A restricted randomization technique will be employed for the within-strata allocation, to ensure the desired balance in cluster number in the study arms. The summary of the trial profile is shown in Fig. 3.

It will not be possible to blind the interviewers who administer questionnaires in the household survey or the respondent female heads of households, because of the pragmatic nature of the trial, as they could acquire treatment knowledge from informal sources or *on the grapevine*. Some of the respondents could also be social group members or providers. It will also not be possible to blind the investigators who administer the intervention or the participants receiving the intervention (social groups and providers).

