Adjusted analysis based on cluster summaries will be done in a two-staged procedure. In the first stage, the covariate-adjusted residual will be obtained for each cluster using standard multiple linear regression analysis, incorporating the stratum (as a fixed effect) and all baseline cluster-level covariates of interest but excluding the intervention effect. The potential baseline covariates of interest will include cluster-level summaries of the primary outcome measure, mean scores for respondents’ knowledge and opinions (about malaria and malaria diagnosis) and other baseline variables found to differ between the study arms and which can be determinants of a particular outcome. Only cluster-level summaries of baseline covariates will be used in the adjusted analysis because baseline and follow-up data will be on different individuals, as the study employed a repeated cross-sectional design [39, 40]. The difference-residual for each cluster will be obtained as the difference between the observed outcome in each cluster and the predicted outcome in the absence of an intervention effect. The covariate-adjusted residuals will replace the cluster-level proportions in the second stage in estimating the intervention effects, which are thus adjusted for the covariates in the first stage.

The same cluster-level methods will be used to evaluate the effect of the interventions on the secondary outcomes. Comparative analysis of baseline data will be used to assess the balance between the treatment arms and potential baseline variables that will be reported include the cluster-level and individual-level summaries of the primary and secondary outcome measures, the age and sex of individual subjects, the age of the respondent female head of household, educational level, occupation, level of knowledge and opinions about malaria and malaria diagnosis and average knowledge and opinion score. Summary statistics of baseline data will be used to assess the level of demand for MRDT, care-seeking practices and pattern of anti-malarial drug use among community members with fever or malaria-like illness; the level of knowledge and opinions of the female heads of households about malaria and malaria diagnosis and the level of knowledge and opinions of healthcare providers about malaria and malaria diagnosis.

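### As written, the baseline survey follows allocation and uses interviewers from whom allocation is not withheld, so the baseline-adjusted estimate is open to arm-dependent reporting

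*Protocol article*

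**What the plan says.** Participant timeline: consent of clusters, social groups and providers is obtained "before clusters are randomly allocated into the three study arms". The next sentence reads "The main study outcomes will then be measured through a baseline household survey" and an end-of-study survey. The stated order is consent, allocation, baseline.

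Randomization: a statistician is "to assign the 18 clusters across the 3 strata to the 3 treatment arms after written consent is obtained from all recruited participants". The trigger is consent, not a finished baseline survey. The restriction on the allocation is there "to ensure the desired balance in cluster number in the study arms".

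Population-based household survey: "The baseline survey will be carried out before the intervention (see Fig. 1". This fixes the survey relative to the intervention only and fits either side of allocation.

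On masking, the Randomization section says "It will not be possible to blind the interviewers who administer questionnaires in the household survey", and gives as the reason "as they could acquire treatment knowledge from informal sources". It does not separate the baseline survey from the end-of-study survey.

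Data analysis: the unadjusted comparison is a stratified t test on cluster proportions. A further two-stage adjusted analysis first regresses the outcome on stratum and baseline covariates, leaving the intervention out, and then compares residuals between arms. "The potential baseline covariates of interest will include cluster-level summaries of the primary outcome measure", mean knowledge and opinion scores, and other baseline variables that turn out to differ between arms.

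**The concern.** The outcome is a caregiver's report of fever and testing over the previous two weeks. Households are screened and give consent during the survey, and ineligible households may be revisited if the quota is short (Sampling technique). If the arm is already known, both who is counted as a case and what is reported could differ by arm. The respondents may themselves be social group members or providers, as the Randomization section notes.

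A baseline distorted in this way would enter the adjusted estimate directly. It could also create the between-arm differences that lead to further covariates being chosen. The reason given for not masking, informal leakage of the allocation, cannot apply to a survey completed before any allocation exists. The stated order therefore gives up a protection that was available.

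**Working it through.** **Order.** No text shown puts the baseline survey before allocation. The timeline puts it after, the randomisation trigger is consistent with that, and the survey section is neutral. Both the timeline and the survey section refer to Fig. 1, which is not available here.

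**Inputs** (Sample size): control proportion 11%; coefficient of variation between clusters within strata k = 0.16; 6 clusters per arm; 40 subjects per cluster, raised to 50. Assumed, because the article gives no figure: a correlation of 0.8 between a cluster's underlying baseline and endline levels, and a baseline over-report of 5 points.

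**The plan's own figure.** For 31% against 51%, two-sided 5%, 80% power and m = 40, c = 1 + 7.849 × [0.31×0.69/40 + 0.51×0.49/40 + 0.16²×(0.31² + 0.51²)] / 0.20² = 1 + 4.06 = 5.06, rounded up to 6. The stated 6 clusters per arm reproduces, and this point does not change it.

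**Chance imbalance at baseline.** With p = 0.11 and m = 50:
- sampling variance 0.11×0.89/50 = 0.00196
- between-cluster variance (0.16×0.11)² = 0.00031
- total 0.00227, so the SD of a cluster proportion is 4.8 points
- difference between two arms: 1.96×√(2×0.00227/6) = 5.4 points
- the part that is true cluster-level difference: 1.96×√(2×0.00031/6) = 2.0 points

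Sampling noise makes up 0.00196/0.00227, about 86%, of the variance.

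**Effect of a biased baseline if there is no true effect.** The expected adjustment slope without bias is 0.8×0.00031/0.00227 = 0.11. A 5-point over-report would then move the estimate by at most about 0.11×5 = 0.55 points. Simulating the two-stage method gives about 0.4, since the bias itself spreads the baseline values and flattens the slope.

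**Effect if both intervention arms truly gain 20 points over control** (simulation, k = 0.16):
- unadjusted estimate: about 20 points throughout
- adjusted, no baseline bias: 18.6
- adjusted, 5-point over-report in both intervention arms: 14.7, a shift of 18.6 − 14.7 = 3.9 points
- adjusted, 5-point over-report in one intervention arm: a shift of about 2 points

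The movement is towards the null. Stage 1 omits treatment, so a baseline that tracks the arm absorbs part of the treatment effect before stage 2 looks for it. The loss from 20 to 18.6 without any bias has the same cause.

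**Sensitivity.** At k = 0.5 (assumed), the corresponding figures are about 2 points with no true effect, and a fall from 18.7 to 12.8 with 20-point effects and both arms biased.

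**The case against.** The order rests on one word, 'then', in a sentence that also covers the end-of-study survey, and the figure that would settle it is not shown. This stands as a limit: the point concerns the text as written. It does not remove the need to settle the order.

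Nothing has been delivered at baseline, so the motive to report differently is weak. Supervisors recheck an average of 30 households per cluster, interviewers are recruited and listed apart from the investigators who run the intervention, and the trial is declared open-label. These points lower the likelihood of bias. They do not amount to withholding the allocation, and the article does not say that supervisors are unaware of the arm.

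A reader might infer several stronger things that the article does not support:
- *That the unadjusted comparison is biased by the baseline.* It uses no baseline data.
- *That the adjusted effect shifts by several points whatever the truth.* That would need a slope of about 0.5 to 0.8. At k = 0.16 the slope without bias is about 0.11; the larger shifts appear only when there is a true effect.
- *That a 5.4-point baseline gap reflects real differences between clusters.* Most of it is sampling noise at this k.
- *That restricting on cluster number alone is an error.* Stratified 2:2:2 allocation is valid. Balancing on the baseline outcome is a refinement, and at k = 0.16 it would largely balance noise.

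**Conclusion.** The point holds as a design weakness in the stated sequence, and it should be corrected. The adjusted estimate is exposed to baseline reporting or case-finding that differs by arm. The unadjusted test is exposed only through unmasked interviewing at the end-of-study survey. Nothing in the article shows that bias occurs, and every size above depends on an assumed 5-point over-report and an assumed correlation of 0.8. On those assumptions, with k = 0.16, the adjusted effect moves by about 0.4 points under no effect and by about 2 to 4 points towards the null under 20-point effects. If Fig. 1 shows baseline before allocation, what remains is a contradiction in the timeline text and the lack of any step to mask the end-of-study interviewers.

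**What to change.** State in the timeline and randomisation sections, and carry out, this order: consent, baseline survey completed in all 18 clusters, then allocation generated and disclosed. Bring the text and Fig. 1 into agreement.

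For both surveys, do not disclose the allocation to interviewers and, where travel allows, avoid assigning an interviewer to clusters of one arm only.

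Optional: with baseline in hand, restrict the allocation on baseline cluster MRDT proportion. There are 6!/(2!2!2!) = 90 allocations per stratum and 90³ = 729,000 in all. In simulation at k = 0.16, keeping the best-balanced tenth holds the spread of observed arm means to about 1.3 points, against a median of 3.2 without restriction.

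Cost: a delay between consent and allocation while every household is enumerated and screened, some extra fieldwork logistics because clusters lie far apart, and masking that will remain imperfect at the end-of-study survey. No more clusters or subjects are needed. The article describes the trial as ongoing, so if the baseline survey has already been done, report the order actually followed and apply the interviewer steps to the end-of-study survey if it is still to come.

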**Fig. 1 Fig1:**
[figure not shown]
Schedule of enrolment, interventions and assessments

### Interventions

The interventions in this study include (1) the sensitization and education of social groups about MRDT (social group intervention) and (2) the sensitization and education of social groups plus the training of healthcare providers in health communication about MRDT with clients (social group/provider intervention). Participants in the control arm will not receive any of these interventions.

### The sensitization and education of social groups

The social group intervention will involve the sensitization and education of social groups within each cluster in the social group arm. There will be three episodes of group discussion/interaction, one per month, with each social group during the intervention period of 3 months. Health education messages designed to change incorrect beliefs and perceptions, promote correct beliefs and perceptions, increase knowledge and promote key actions will be communicated to social group members in an interactive session/group discussion. The health education message is adopted from a national framework [42] and modified for the study.

Each discussion will be a 1-hour event. One investigator will moderate each discussion with a group discussion guide. In order to make the intervention more pragmatic and to optimize adherence to the trial intervention, the discussions will take place at the usual meeting time of each social group, or at an agreed time, and at their usual meeting point/venue or at a central location as is most convenient for the participants. The intervention will be discontinued for a social group or cluster whenever such a request is made by the respective social group head/leader or cluster head/authority. The first episode will be divided into 7 sub-headings, viz. (1) introduction, (2) individual beliefs and opinions, (3) key facts about malaria, (4) key facts about MRDT, (5) demonstration of testing with MRDT kit, (6) key actions to practice and promote and (7) closing remarks. The moderator will explain the research problem and objectives to the participants and the broad role the participants (social group members) are expected to play in addressing the problem. Each participant will then share his/her beliefs and opinion about malaria with respect to the cause, symptoms, complications/fatalities, diagnosis, treatment, where to seek care and why and prevention. The discussion will explore the reasons for and against these views and there will be questions and answers from participants. The moderator will then highlight the key facts about malaria. Key facts about the MRDT will also be highlighted and discussed. Malaria rapid diagnostic test (MRDT) will be demonstrated in volunteer participants, the procedure will be explained, the results interpreted and explained to them and those that test positive will be treated with an ACT.

The moderator will then highlight and discuss the key actions that the participants should exercise and promote as individuals, social group members, opinion leaders, parents, heads of households, family members, friends and relatives, neighbours, etc. These actions include recognizing the symptoms of malaria especially in children under 5 years of age, promptly seeking care with providers that carry out MRDT (preferably in the public primary health facilities) and requesting the “simple test” for malaria (MRDT), receiving the test, asking for the result, and receiving treatment for malaria (with ACTs) only when the test is positive, making sure children under 5 years of age receive treatment within 24 hours of on-set of fever and acquiring and giving the appropriate ACTs at the correct dose for the correct number of days. The moderator will then make closing remarks and thank the participants for their time.

The second and third episodes will take a similar format as the first but will focus more on re-emphasizing the key facts and actions to practice and promote so as to reinforce participants’ knowledge and attitudes. The participants will be encouraged to share their experiences in the preceding 4 weeks for discussion and clarification. Visits to the social groups will end with the third episode of group discussion. However, group members will be able to contact the investigators on their cell phones if they still require clarification on malaria and MRDT during the subsequent months.

Other supportive interventions will include reminder text messages sent at least weekly to social group members that have cell phones, regular phone calls to social group heads (to urge them to remind and encourage the group members during meeting sessions) and regular visits by a provider (PMV or public) to the scheduled meetings of each social group for provision of MRDT services and ACTs for positive results.

### The training of healthcare providers

The clusters in the social group/provider arm will also receive the social group treatment as described above and in addition, will receive provider training in health communication about MRDT with clients. Health communication involves the use of communication strategies to inform and influence individual and community decisions that enhance health and it is a vital aspect of provider-patient relations [43]. The provider training will involve a one-day sensitization and training workshop for the participating healthcare providers in Abakaliki (the capital of Ebonyi state). The research team will administer the workshop with the aid of a PowerPoint slide presentation, a provider training guide and a health communication guide. There will be a pre-post-test to assess the knowledge of participants about malaria, MRDT and communication. The training will be divided into two parts with 4 sessions in each. The first part will focus on sensitizing the participants. The 4 sessions include (1) pre-test, (2) background information on the research problem and aim (objectives) and on malaria, (3) demonstration of testing using the MRDT kit and (4) key actions to practice and promote. The facilitators of the training will use a PowerPoint slide presentation to highlight the objectives of this part of the workshop and then to present an explanation of the problem the research is designed to address and how, the research objectives and the broad role the participants/providers are expected to play in this respect. Volunteer participants will then perform and receive MRDT, explain the procedure and interpret the results. This will be followed by a question and answer session on the sensitivity and specificity of MRDT, adherence to test results and what to do if result is negative and the benefits of universal testing and complete adherence to the test results. The facilitators will then highlight the key actions that need to be practiced and promoted by providers. Questions and comments will be respectively answered and discussed.

The second part of the training will focus on improving the health communication skills of participants with the aid of a health communication guide. The 4 sessions in this part include (1) background information on health communication, (2) a practical session (including simulation) on health communication with clients, (3) a closing session and completion of assessment forms and (4) post-test. The facilitators will use a PowerPoint slide presentation to highlight the objectives of this part of the workshop and to talk about communication and health communication with regards to definitions, communication components, process, channels/media, types, aids, etc. This will be followed by a practical session and simulation of a real-life situation. The facilitators will then divide the participants into two groups – the public provider group and the private provider group. Each group will be sub-divided into clients and providers. Each client/patient sub-group will visit their respective providers with malaria-like illness. Their providers will then engage them in health communication about malaria and MRDT (with or without the use of a self-written/improvised guide). The strengths and weaknesses of each group’s communication techniques during the simulation will be noted by the other group. These will be read out by a facilitator for discussion by all parties.

The facilitators will then introduce the participants to a health communication guide on how to effectively educate their clients during the discharge of their duties. They will be educated on how to use the guide in communicating with all categories of clients including those that requested MRDT or freely accepted providers’ suggestion of a test or initially declined to receive the test. The participants will then apply the guide in another round of simulation exercise. Participants will then complete an assessment form on which they will rate the training process and logistics, state what they believed or knew previously that has now been corroborated, what they believed or knew previously that has now been contradicted, what they just learnt for the first time and any additional key actions that can be taken or promoted to increase the use of MRDT and adherence to test results. The participants will be encouraged to use the health communication guide to effectively communicate with their clients (suspected malaria cases) about MRDT at the course of their regular duties. A facilitator will then give the closing remark and implore the participants to develop their communication skills by putting it to practice immediately.

The training workshop will be followed by a twice weekly reminder text message and a monthly visit to each of the participating providers for supportive supervision (on-the-job training) and monitoring throughout the rest of the 3-month intervention period. Each support visit will be aimed at assessing providers’ performance, exploring their experiences in the previous weeks and addressing their challenges in health communication with their clients. The on-the-job training will make the intervention more pragmatic and will optimize adherence to the trial intervention. The healthcare provider’s intervention will be discontinued whenever requested by the respective provider.

The trained providers will also be subjected to mystery client monitoring. The mystery client assessment of providers’ performance will guide the researchers in properly identifying those that require more attention, and in what specific areas, during the support visits. Mystery clients will be trained on how to interact with providers and how to complete the assessment form thereafter. A mystery client will visit a participating provider/health facility and claim he has malaria based on familiar symptoms. If proposed by the provider, he/she will freely accept MRDT, otherwise, he/she will request MRDT. He/she will all the while note whether the provider engaged him/her in health communication with basic standard techniques. He/she will then complete the assessment form after leaving the provider. Each provider/health facility will be visited by a mystery client at least twice.

